#### Cross-sectional study

2.3.1

##### Main criterion: concordance between professional assessments

2.3.1.1

To meet the main objective, the concordance of the results of the neuropsychological assessment, RDA and multiprofessional evaluation will be studied in pairs (agreement between professional assessments). Each professional involved in the study will give a “favorable,” “reserved” or “unfavorable” opinion based on their practice. Evaluation criteria will correspond to cross-tabulated numerical values of results from each assessment tool studied (neuropsychological assessment, RDA and multiprofessional evaluation). “Reserved” opinions indicating driving restrictions will initially be classified as “unfavorable,” so that the results can be expressed as a binary Favorable/Unfavorable variable for each assessment. The RDA results will also include the number of driving instructor interventions on pedals, steering wheel and other car controls, using categorical variables. The values *a*, *b*, *c* and *d* (Table 1) will be used to perform the concordance test detailed in the next section (“Statistical analysis”).

**Table 1 tab1:** Evaluation criterion of the main objective for contingency table.

		Assessment x_i_	
		Favorable	Unfavorable
Assessment x_ii_	Favorable	*a*	*b*
	Unfavorable	*c*	*d*

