Each rehabilitation center will recruit around 10 to 20 patients, up to a total of 100 participants. A post hoc sensitivity analysis was performed using G*Power Software Version 3.1.9.7 (Faul et al., 2007) to determine the minimum effect size that could be achieved with 100 participants. A post hoc power analysis for an independent-sample t-test was conducted assuming one-tailed testing. For effect size varying from large (d = 0.8) to small (d = 0.2), 80% power and alpha error probability of α = 0.05 a sample size interval of at least 12 to 156 participants is suggested. With a sample of 100 participants to be included in this study and 80% power the effect size is estimated at 0.25. Each participant must have a npABI and be between the ages of 21 and 65, in order to avoid confusing the issues of ageing and non-progressive acquired brain injury, people over 65 were excluded from the study and treated at their center for routine care. All participants must have held a Category B driving license (light vehicles) for at least 3 years and have driven a minimum of 10,000 km, so as not to assess novice drivers. They have been examined by the PRM doctor, who confirms that there are no contraindications to driving other than the pathology under study. They also gave their consent to take part in the PREVAC study. The ethical committee has classified this research as a non-interventional, involving no risk or constraint for participants, and in which all procedures are carried out in the usual way. They must not have a medical condition (other than npABI) that is incompatible with maintaining their driving license, according to the list of conditions mentioned in the decree of March 28, 2022. They must not have any oral comprehension disorders that can be perceived by the therapist, must not be pregnant (to avoid an interruption of pregnancy in the event of an accident and the resulting psycho-social and legal risks), and must not be under the influence of any Level 3 medication that could present a driving risk.

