##### Multiprofessional synthesis

2.2.1.5

Professionals then work together to issue a joint opinion (favorable, unfavorable or reserved) on the participant’s driving ability, based on the assessments carried out.

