##### Approved doctor visit

2.2.1.7

Following the multiprofessional evaluation, participants then have to undergo a consultation with an approved doctor from their department. They then inform the study investigator of the opinion issued by the approved doctor (fitness, temporary fitness and/or with restriction(s), unfitness).

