###### Secondary criterion A: concordance professional assessment / approved doctor’s opinion

2.3.1.2.1

Evaluation criteria for secondary objective A will be those used for the main objective, crossed with those of the approved doctor’s opinion, expressed as a binary variable Fit / Unfit to resume driving (Table 2).

**Table 2 tab2:** Evaluation criteria of the secondary objective A for contingency table.

		Assessment x_i_	
		Favorable	Unfavorable
Approved doctor’s opinion	Fit	*a*	*b*
	Unfit	*c*	*d*

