#### Statistical analysis

2.3.3

To meet the main and secondary A and B objectives, concordance tests will be used to verify that two independent abilities to resume driving measures (two tests) of the same modality—“Favorable” or “Unfavorable”—are equal. Concordance analyses between tests (binary variables) will be expressed in the form of concordance percentages, simple kappa coefficient and its 95% confidence interval. Analyses between TRIP (continuous variable) and other tests (binary variables) will be conducted using *t*-tests or Mann–Whitney tests depending on the TRIP score distribution. Multivariate regression will also be used to study measures’ concordance and prediction levels, for both objectives. It will be logistic or linear, depending on the studied variable (i.e., approved doctor’s opinion for objective A and TRIP results for objective B).

A sensitivity and specificity analysis of the approved doctor’s opinion will also be carried out. Performance metrics (Secondary Objective C) will be calculated from the confusion matrix values (Table 4):$$\mathrm{Accuracy:}\frac{RP+RN}{RP+RN+FP+FN}$$$$\mathrm{Sensitivity (Se):}\frac{RP}{RP+FN\text{.}}$$$$\mathrm{Specificity (Sp):}\frac{RN}{FP+RN}$$$$\mathrm{Positive predictive value (PPV) or Precision (Pr):}\frac{RP}{RP+FP}$$$$\mathrm{Negative predictive value (NPV):}\frac{RN}{FN+RN}$$

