### Expected results

2.4

As this is an exploratory study, no assumptions are made concerning concordances between the different professional opinions. However, in light of the literature concerning coping strategies used by people with npABI, we can expect some results:

In the event of an unfavorable opinion on the neuropsychological assessment and a favorable opinion on RDA, we should observe high compensation scores on the TRIP, as well as a low score on the BIDSAM, indicating good metacognition enabling the driver to adapt their driving to their difficulties.

In the event of an unfavorable opinion on both the neuropsychological assessment and RDA, we should observe low compensation scores on the TRIP and a high score on the BIDSAM, indicating a low awareness of difficulties that does not allow the use of compensatory strategies.

TRIP compensation scores and the BIDSAM score should be good predictors of road risk.

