### Longitudinal study

3.2

Thanks to the longitudinal study, further analyses will enable us to measure the relevance of the multiprofessional evaluation by comparing each assessment with the road risk. Assessments that are significantly correlated with perceived road risk (as well as with self-reported accident rates) can be considered as good predictors of road risk, further supporting their relevance.

The longitudinal study will also shed light on any changes in driving habits adopted by participants since regularization of their driving license. These analyses will quantify the adoption of coping strategies related to npABI sequelae. Complementary analyses would also enable us to study relationships between changes in driving habits and various assessment scores. For example, a high correlation between changes in driving habits and BIDSAM would highlight the link between metacognition and behavioral regulation (adjusting driving to compensate for cognitive sequelae).

Lastly, this longitudinal study will provide some answers to the HAS recommendation that people with npABI be given the best possible support to resume or stop driving. By questioning participants, the support for resuming driving questionnaire will highlight the self-reported relevance of multiprofessional assessment for:- Judging their driving ability- Becoming aware of their driving ability- Obtaining information and advice from the team- Adjusting their driving (in the case of unrestricted fitness to drive)- Understanding the reasons for unfitness to drive or driving restrictions (in the case of fitness with restriction codes)- Dissuading them from driving (in the event of unfitness)

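### Criterion A: reserved opinions are coded unfavorable, but the doctor's restricted-fitness level has no stated place in Fit/Unfit, so matched judgments can count as disagreement

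*Protocol article*

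**What the plan says.** Four places in the protocol article bear on this.

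- **Team opinions.** The multiprofessional opinion has three levels (Section 2.2.1.5: "Professionals then work together to issue a joint opinion (favorable, unfavorable or reserved) on the participant"), as do the neuropsychological and on-road opinions. For analysis, Section 2.3.1.1 states that reserved "opinions indicating driving restrictions will initially be classified as" unfavorable.
- **Doctor's opinion.** Section 2.2.1.7 also records three levels: "fitness, temporary fitness and/or with restriction(s), unfitness".
- **Criterion A.** Section 2.3.1.2.1 crosses each team opinion with the doctor's opinion, "expressed as a binary variable Fit / Unfit to resume driving" (Table 2). No rule is given for the doctor's middle level.
- **Statistics.** Under Section 2.3.3, concordance analyses "will be expressed in the form of concordance percentages, simple kappa coefficient and its 95% confidence interval". The same section plans a logistic regression with the doctor's opinion as the outcome.

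Criterion C (Section 2.3.2.1) reuses the pairing: favorable for the team and fit for the doctor are both treated as a prediction of no increased road risk.

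**The concern.** The article fixes where one rater's middle level goes and leaves the other's open. Its own vocabulary treats the doctor's middle level as a kind of fitness. Section 2.2.1.7 names it so, and Section 3.2 lists "in the case of fitness with restriction codes" separately from unfitness. On that reading, a team and a doctor who both conclude that the person may drive under restrictions are recorded as Unfavorable and Fit. That is cell *b* of Table 2, and simple kappa gives it no partial credit.

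The article plans to draw conclusions from such disagreement:

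- Section 3.1.1 would conclude that the neuropsychological assessment is not a reliable predictor.
- Section 3.1.2 would raise questions about the value of the on-road assessment.
- Section 3.1.3 would take the case as one where an opinion is hard to form.

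A coding artifact would feed all three. In criterion C, the same restricted driver could be a predicted positive for the team and a predicted negative for the doctor, so their sensitivities and specificities would not be comparable.

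**Working it through.** The article states no agreement figure to reproduce; Section 2.4 says that "no assumptions are made concerning concordances between the different professional opinions". The check therefore follows the coding rules and then illustrates their effect.

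**Inputs.** N = 100 is taken from Section 2.1 ("up to a total of 100 participants"). The shares of the three levels are assumptions. Perfect three-level agreement between team and doctor is also assumed, so any disagreement comes from coding alone.

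**Layout.** Let F, R and U be the counts of matched favorable/fit, reserved/restricted-fit and unfavorable/unfit.

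- Restricted fitness coded Fit: *a* = F, *b* = R, *c* = 0, *d* = U.
- Restricted fitness coded Unfit: *a* = F, *b* = 0, *c* = 0, *d* = R + U.

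**Formulas.** Observed agreement po = (a + d)/N. Chance agreement pe = [(a + b)(a + c) + (c + d)(b + d)]/N². Kappa = (po − pe)/(1 − pe).

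**Restricted fitness coded Fit, 60/20/20.** po = 0.80. pe = 0.8 × 0.6 + 0.2 × 0.4 = 0.56. Kappa = 0.24/0.44 = 0.545 (large-sample 95% CI 0.39 to 0.70).

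**Restricted fitness coded Fit, 50/30/20.** po = 0.70. pe = 0.8 × 0.5 + 0.2 × 0.5 = 0.50. Kappa = 0.20/0.50 = 0.40.

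| F/R/U | Concordance, coded Fit | Kappa, coded Fit | Concordance and kappa, coded Unfit |
|---|---|---|---|
| 60/10/30 | 90% | 0.78 | 100%, 1.00 |
| 60/20/20 | 80% | 0.55 | 100%, 1.00 |
| 50/20/30 | 80% | 0.60 | 100%, 1.00 |
| 50/30/20 | 70% | 0.40 | 100%, 1.00 |
| 40/40/20 | 60% | 0.29 | 100%, 1.00 |
| 40/50/10 | 50% | 0.14 | 100%, 1.00 |

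Under these assumptions concordance falls by exactly R/N. If half of the restricted cases were coded each way, kappa would be 0.80 for 50/20/30 and 0.70 for 50/30/20.

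**Without perfect agreement.** Moving the doctor's middle level from Unfit to Fit changes the number of concordant cases by n(restricted, favorable) − n(restricted, reserved) − n(restricted, unfavorable). Each matched restricted case still costs one agreement. The net change also depends on how often restricted fitness meets a favorable or an unfavorable team opinion.

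**Main criterion.** The neuropsychological, on-road and multiprofessional opinions all follow the Section 2.3.1.1 rule. A reserved-reserved pair is therefore concordant, and no mismatch of this kind can arise.

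**The case against.** The strongest reply is that the article never codes restricted fitness as Fit. It only announces a binary variable, and the other mapping removes the loss completely. Section 2.1 says the protocol and case report form are deposited publicly, and they may hold the rule. This stands as far as it goes: the low kappas follow from a reading, not from a stated instruction. It does not dispose of the point. The article states a rule for one rater only, and its own wording for the other points the opposite way.

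Three stronger readings are tempting but not supported.

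- **That the two middle levels are the same judgment.** They are similar but not shown to be identical. The doctor's level includes temporary fitness, which need not carry a restriction. Section 2.2.1.8 groups reserved with unfavorable opinions for support, and mentions driving-cab changes under a favorable opinion. A favorable opinion could therefore properly meet restricted fitness.
- **That the main criterion is biased in the same way.** Its three opinions share one coding. Counting reserved-unfavorable as agreement and reserved-favorable as disagreement is what any such dichotomization does. Preferring another statistic there is a matter of taste in an exploratory study.
- **That the study discards the restricted level.** Section 2.3 promises description of every variable by category and possible subgroups by the conclusion of the medical examination. Section 3.2 keeps restricted fitness separate in the support questionnaire. The loss is confined to the binary tables and the analyses built on them.

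The word initially in Section 2.3.1.1 hints at a later recoding. None is described, and it concerns the team opinions only.

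**Conclusion.** The point holds for secondary criterion A, its logistic regression and the team-doctor comparison in criterion C. Sections 2.2.1.7, 2.3.1.1 and 2.3.1.2.1 together leave the result dependent on an unstated choice, and the wording favors the option that creates disagreement. Under perfect three-level agreement and that option, the loss in concordance equals the share of matched restricted cases. With assumed shares of 20% to 30%, kappa is between 0.40 and 0.60 in the examples shown instead of 1.00. These are illustrations at the unfavorable end: they assume that every restricted case is coded Fit, and the true share is unknown. Where every restricted-fitness case is paired with a reserved opinion and coded Fit, a larger sample would not remove the loss.

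**What to change.** Before results are seen, reconcile Sections 2.2.1.7, 2.3.1.1 and 2.3.1.2.1 so that one dichotomization rule covers team and doctor in criteria A and C, including the regression on the doctor's opinion. The sponsor should decide which side the middle level falls on. If the choice departs from the Section 2.3.1.1 rule for reserved opinions, the text should say so.

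For criterion A, report the full 3x3 table with linearly weighted kappa (weights 1, 0.5 and 0 for a difference of zero, one or two levels). As a sensitivity analysis, give binary kappa under both collapses: middle level with favorable/fit for both raters, and middle level with unfavorable/unfit for both.

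The main-criterion binary kappa can stay, with a 3x3 weighted kappa as an optional supplement.

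The cost is a few sentences of analysis text, since all three levels are already recorded. The downside is some sparse cells at about 100 participants and one more table to report.

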##### Secondary evaluation criteria (criteria A and B)

2.3.1.2

A cross-sectional analysis of professional evaluations will be performed to meet the following secondary objectives:Study the concordance between each professional assessment (cf. main objective) and the approved doctor’s opinion concerning the participant’s ability to resume driving;Study the concordance between professional assessments (cf. main objective) and the TRIP

###### Secondary criterion A: concordance professional assessment / approved doctor’s opinion

2.3.1.2.1

Evaluation criteria for secondary objective A will be those used for the main objective, crossed with those of the approved doctor’s opinion, expressed as a binary variable Fit / Unfit to resume driving (Table 2).

**Table 2 tab2:** Evaluation criteria of the secondary objective A for contingency table.

		Assessment x_i_	
		Favorable	Unfavorable
Approved doctor’s opinion	Fit	*a*	*b*
	Unfit	*c*	*d*

###### Secondary criterion B: concordance professional assessment / TRIP grid

2.3.1.2.2

An analysis identical to the main objective will be carried out, cross-referencing the results of the professional assessments with that of the TRIP, expressed as a binary variable Favorable / Unfavorable (Table 3).

**Table 3 tab3:** Evaluation criteria of the secondary objective B for contingency table.

		Assessment x_i_	
		Favorable	Unfavorable
TRIP grid	Favorable	*a*	*b*
	Unfavorable	*c*	*d*

The TRIP score will also be analyzed continuously (total adjusted score out of 100), in total and by sub-score. Correlation analysis will also be carried out between the raw results from the neuropsychological tests and the TRIP grid, in order to identify the neuropsychological tools most predictive of driving ability in real-life situations.

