##### Neuropsychological assessment

2.2.1.2

This assessment is carried out by a psychologist specialized in neuropsychology. It includes a series of validated standardized tests investigating attentional, executive and psycho-behavioral functions. The list of tests was co-constructed according to different criteria:- psychometric qualities (sensitivity, validity, reliability)- relevance established in the literature in relation to driving ability evaluation- availability and frequency of use in current practice (assessed through a survey of rehabilitation centers)- administration conditions (essentially non-verbal tests for use with patients with expressive aphasia; non-bimanual tests allowing inclusion of patients with hemicorporeal deficits; duration deemed acceptable and equipment easy to obtain and use).

The neuropsychological assessment lasts around 3 h, divided into two one-and-a-half-hour sessions, each with a five- to ten-minute break. The order of administration of the tests was established so as to alternate tasks according to their format (computerized vs. paper-and-pencil), their mental load (higher or lower), their sensitivity to fatigue, and the cognitive functions called upon. The standardized neuropsychological assessment protocol is described in the case report form. It includes the following tests: Alertness (TAP 2.3.1), Divided attention (TAP 2.3.1), Epworth scale, Trail-Making-Test (TMT), Go/Nogo (TAP 2.3.1), Basic Empathy Scale in Adults (BES-A), Neglect with central task (TAP 2.3.1), Tour of London (TOLDX 2^nd^ edition), Working memory difficulty level 3 (TAP 2.3.1), Sustained attention color-or-form version (TAP 2.3.1) and UPPS Impulsive Behavior Scale. Lastly, the Brain Injury Driving Self-Awareness Measure—BIDSAM (Gooden et al., 2017) is part of the neuropsychological assessment, but will be completed following the RDA.

For each test, the examiner collects raw and standardized scores (each participant’s performance is compared to the standard group). Based on this assessment, the neuropsychologist then issues an opinion (favorable, unfavorable or reserved) on the estimated compatibility between the participant’s cognitive functions and the return to driving.

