#### Relevance of the neuropsychological assessment

3.1.1

- In the event of concordance between the neuropsychologist’s opinion and other assessments (RDA, multiprofessional, approved doctor’s opinion), the neuropsychological assessment can then be considered to be a good predictor of driving ability, particularly by shedding light on the driving restrictions to be recommended.- In the event of a discrepancy between the neuropsychologist’s opinion and other assessments (RDA, multiprofessional, approved doctor’s opinion), the neuropsychological assessment cannot be considered a reliable predictor of driving ability, in line with the mixed findings reported in the literature (Wolfe and Lehockey, 2016; McKay et al., 2016; Ortoleva et al., 2012). However, this assessment will still be of obvious interest for detecting any reduction in useful field of view, raising awareness of certain deficits, or suggesting rehabilitation options adapted to the person’s cognitive profile. The neuropsychologist’s role is decisive in the project to resume driving (Perna et al., 2021).- Neuropsychological tests whose scores are significantly correlated with the TRIP score can be considered the most predictive of driving ability. These results will help guide the choice of neuropsychological tools.

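### Tests are labelled most predictive from raw-score correlations with TRIP alone, a rule that cannot separate a test that adds information from one that only tracks age between 21 and 65

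*Protocol article*

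**What the plan says.** Section 2.3.1.2.2 of the protocol article fixes the type of score: "Correlation analysis will also be carried out between the raw results from the neuropsychological tests and the TRIP grid". It also gives the purpose: "in order to identify the neuropsychological tools most predictive of driving ability in real-life situations".

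Section 3.1.1 gives the rule for reading the result: "Neuropsychological tests whose scores are significantly correlated with the TRIP score can be considered the most predictive of driving ability". The stated use follows: "These results will help guide the choice of neuropsychological tools".

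Four other places bear on the point.

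- **Section 2.1 (age range).** "Each participant must have a npABI and be between the ages of 21 and 65". People over 65 are left out "in order to avoid confusing the issues of ageing and non-progressive acquired brain injury". This restriction is the only control for age that the article states.
- **Section 1.1 (age as a risk factor).** Age is the first item in its list of influences on road risk after brain injury.
- **Section 2.2.1.2 (standardized scores).** "For each test, the examiner collects raw and standardized scores". The standardized scores come from comparison with a standard group, and the article does not say whether that group is matched on age. Only the raw results are named for the correlation.
- **Section 2.3.3 (regression).** A multivariate regression is planned for objectives A and B, with TRIP results as the outcome for B. The article does not name its covariates.

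**The concern.** Timed attention, reaction-time and trail-making scores may well change with age across a 44-year span, and on-road performance may too. If both do, a test and TRIP will correlate even when the test says nothing about driving once age is known. Section 3.1.1 asks only whether the correlation is significant, so it treats such a test exactly like one that carries information of its own.

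This matters because the result is meant to be used. Section 3.1.1 ties it to the choice of tests, and section 3.4.2 speaks of finding the best-performing tools in support of public policy. Age is known for every patient at no cost, whereas the test battery takes about three hours. A centre choosing tests would want to know which ones tell it more than the date of birth does. The article itself regards age as a competing explanation, since it restricts eligibility on that ground, but the selection rule does not carry that reasoning through.

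**Working it through.** **The plan's own figure.** There is none to reproduce. The sample-size paragraph in 2.1 concerns a t-test and gives no figure for a correlation.

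**Inputs from the document.** n = 100 (section 2.1, where it is an upper limit). Significance level 5% (section 2.3). Age 21 to 65, so the span is 65 − 21 = 44 years.

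**Assumptions.** The correlation test is two-sided, because the article does not state sidedness. Write a for the correlation of age with a raw test score and b for the correlation of age with TRIP. The article gives neither, so I take a from 0.3 to 0.5 and b from 0.2 to 0.4. All 100 participants have both measurements.

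**Step 1: the threshold.** A correlation is significant when |r| ≥ t / √(n − 2 + t²), where t is the 97.5% point of the t distribution on 98 degrees of freedom, 1.984. This gives 1.984 / √(98 + 3.938) = 0.197.

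**Step 2: the correlation that age alone induces.** If the test and TRIP are related only through age, the expected raw correlation is a × b.

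- Lowest: 0.3 × 0.2 = 0.06
- Middle: 0.3 × 0.4 = 0.12 (also 0.4 × 0.3)
- Highest: 0.5 × 0.4 = 0.20

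**Step 3: how often such a test is flagged.** In the Fisher approximation, atanh(r) × √(n − 3) is about normal with unit variance, and √97 = 9.849.

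- r = 0.06: 0.0601 × 9.849 = 0.592. P(Z > 1.960 − 0.592) + P(Z < −1.960 − 0.592) = 0.086 + 0.005 = 9.1%.
- r = 0.12: 0.1206 × 9.849 = 1.188. 0.220 + 0.001 = 22.1%.
- r = 0.20: 0.2027 × 9.849 = 1.997. P(Z > −0.037) = 51.5%.

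**Step 4: check by simulation.** There were 20,000 simulated studies per cell, with age uniform on 21 to 65 and the test and TRIP linked only through age.

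| a (age, test) | b (age, TRIP) | expected raw r | flagged, raw | flagged, age-partial |
|---|---|---|---|---|
| 0.3 | 0.2 | 0.06 | 8.7% | 5.0% |
| 0.3 | 0.3 | 0.09 | 14.8% | 5.1% |
| 0.3 | 0.4 | 0.12 | 21.9% | 5.0% |
| 0.4 | 0.4 | 0.16 | 35.5% | 5.1% |
| 0.5 | 0.3 | 0.15 | 31.9% | 5.0% |
| 0.5 | 0.4 | 0.20 | 51.8% | 4.9% |

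The simulation agrees with the approximation. In every simulated cell where a or b was zero, the raw analysis was flagged in about 5% of studies (4.7% to 5.2%). Wider assumptions widen the range: a = b = 0.2 gives 7.0%, and a = 0.6 with b = 0.5 gives 87.2%.

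**Step 5: what adjustment does.** The age-partial correlation is (r − a × b) / √((1 − a²)(1 − b²)). When r = a × b the numerator is zero, which is why the last column stays at about 5%. The price is one degree of freedom: the threshold moves from 0.197 to 0.198.

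**The case against.** The strongest reply is that the aim is prediction, not attribution. TRIP is a score out of 100, and the article does not describe it as age-normed. If slower processing at 60 makes driving worse, a raw score that picks this up is validly predictive, whatever caused the slowing. This stands. It would be wrong to infer that using raw scores is itself an error, or that a test should be barred from recommendation because its association weakens after age adjustment.

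Second, the multivariate regression on TRIP in 2.3.3 may include age, and an article commonly leaves the covariate list to the full protocol. This also stands in part. A reader might infer that the study will not adjust for age anywhere; the document does not say that. Adjustment is absent only from the correlation as described and from the rule built on it. Because 3.1.1 ties the label to correlation, an age-adjusted regression would not change the label as the rule is written.

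Third, a reader might see the over-65 exclusion as contradicting the raw-score analysis. It does not. It is an eligibility restriction, which is a form of control, and it makes no promise about test selection within the eligible range.

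Fourth, the size is wholly assumed, and the tests were chosen partly because the literature links them to driving, so a test related to TRIP only through age is an extreme case. Agreed: the figures show what the rule would permit, not what will happen.

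Finally, this is an additional analysis within a secondary criterion of an exploratory study, and 3.1.1 is worded with caution. That limits the weight of the point but does not remove it, since the result is still meant to guide the choice of tools.

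**Conclusion.** The point holds in a limited form. The article fixes raw scores for the correlation and makes significance the only stated ground for the label, so the rule cannot tell a test that adds to age from one that merely follows it. Under the assumed age correlations, a test of the second kind would be flagged in about 9% to 52% of studies at n = 100, against 5% with age partialled out. That range requires both the raw score and TRIP to vary with age between 21 and 65, and a test with no other link to TRIP.

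The document does not support the stronger readings that raw scores are the wrong choice, that the study has no age-adjusted analysis, or that standardized scores would settle the matter. The fault is that no stated age-adjusted result enters the decision. It is a minor improvement, and confidence in its practical size is low.

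**What to change.** 1. In 2.3.1.2.2, keep the raw correlation and report beside it, for each test, the age-partial correlation with TRIP and its 95% confidence interval. Naming age as a covariate in the regression on TRIP in 2.3.3, with the test score as predictor, would serve equally well.
2. Add the standardized-score correlation as a supplement only. The norms are not stated to be age-specific, so it may not remove age.
3. Amend 3.1.1 so that the choice of tools considers both the raw and the age-adjusted result. A test whose association disappears after adjustment would be reported as predictive in raw form but not shown to add to age.

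**Cost.** The change repeats correlations already planned, on scores and ages already available. It adds a little analysis and loses a little precision, and some tests may receive a more qualified label. No planned result is removed.
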